### Data storage

All data gathered during this study will be stored in compliance with the European Union General Data Protection Regulation (EU GDPR). Data collection will be conducted by authorized investigators using two-factor authenticated, password-protected web-based interfaces, ensuring secure access. To further safeguard participant privacy, all data will be assigned a unique four-digit study code that cannot be linked back to the participant’s identity. Participants can withdraw their consent for the current use of their data, as well as for use in future research, at any time without consequences.

### Sample size calculation

To achieve the primary objective of the study, at least 168 participants are estimated to be needed for random allocation into the two treatment arms (84 per group). The study is designed to have 90% power and a type 1 error of 0.05 for the detection of a between-group difference in MMD of 2 days. Based on previous studies on preventive therapy, we expect a standard deviation (SD) of 4.0 days for the MMD.$$n(\mathrm{number}\;\mathrm{needed}\;\mathrm{per}\;\mathrm{group})=\left(1.96+1.28\right)^2\times\left(\left(2\times\text{SD}^2\right)/\left(\text{diff}^2\right)\right)$$$$n = 10.5 \times \left(32/4\right) = 84$$

Considering potential drop-out, we aim to include *n* = 90 participants per treatment group (*n* = 180 in total) (Fig. 1).

### Outcome measurements

An intention-to-treat approach (all participants who were randomly assigned and received at least one dose of study drug) will be used for the primary analysis. In addition, an as-treated analysis will be performed with only those participants who used study medication daily during three months (without a stop week and estrogen supplementation). A *p*-value less than 0.05 will be considered significant. All statistical analysis will be performed using R.

The primary endpoint is change in MMD from baseline to the last 4 weeks of treatment (weeks 9–12). Group differences (ethinylestradiol/levonorgestrel 30/150 μg versus vitamin E 400 IU) will be analyzed using a mixed-effects model of repeated measures with patients’ baseline value and treatment as fixed effects and patients as random effects. Secondary continuous efficacy endpoints will be analyzed using a linear mixed-effects model including appropriate terms and covariates. The adjusted mean change from baseline for each treatment group, associated 95% confidence intervals, and *p*-values will be reported. Dichotomous endpoints derived from corresponding continuous endpoints will be analyzed with stratified Cochran-Mantel–Haenszel tests. For dichotomous efficacy endpoints, adjusted odds ratios for ethinylestradiol/levonorgestrel compared with vitamin E, associated 95% confidence intervals, and *p*-values will be reported. The primary end point and continuous secondary end points will be analyzed without any imputation of missing data. Sensitivity analyses will be conducted with imputation under missing-at-random or missing-not-at-random assumptions. The data analyst will be blinded.

Safety analysis will include all participants who received at least one dose of study drug. AEs and SAEs will be coded and summarized by Medical Dictionary for Regulatory Activities. All adverse events will be documented.

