## Methods

The primary objective of this randomized controlled trial is to investigate the efficacy of continuous daily use of ethinylestradiol/levonorgestrel (30/150 μg/day) compared to vitamin E (400 IU/day) in treating menstrual migraine. This study follows the latest protocol, dated August 1, 2022, version 5.0. This trial employs an open-label randomized controlled design due to ethical and practical considerations regarding the use of a placebo-controlled study with a combined oral contraceptive pill. However, a control group with an alternative treatment, vitamin E (400 IU/day, soft gel capsules), was included to account for potential confounding biases such as treatment expectations and placebo and nocebo effects. Our patient focus group panel was highly in favor of using vitamin E as a comparator treatment for hormonal intervention. Given the nature of the interventions, participants, investigators, and study personnel are aware of the treatment assignments. Blinding is not feasible in this trial due to the distinct characteristics of the interventions and the practical challenges associated with a placebo-controlled study involving a combined oral contraceptive pill. The study design is visualized in Fig. 1. All endpoints are defined as the mean change from baseline (week − 4 to 0) in a 28-day period as assessed at the 12-week timepoint (week 9 to 12). The primary efficacy endpoint for the trial is the mean change in mean monthly migraine days (MMD) from baseline to the 12-week timepoint. An automated algorithm based on ICHD-3 criteria verifies for each day whether criteria for headache and migraine are met [24–26]. Secondary efficacy endpoints are defined as the mean change from baseline to the 12-week timepoint and include the number of monthly headache days (MHD), migraine attacks, and the amount of 50% responders, defined as patients who had ≥ 50% reduction in the number of migraine days. Secondary safety endpoints are the occurrence of adverse events and serious adverse events. Finally, exploratory endpoints are defined as the mean change from baseline in a 28-day period as assessed at the 12-week timepoint (weeks 9–12). The prespecified exploratory endpoints for this trial are as follows: (1) the amount of 75% responders, defined as patients who had ≥ 75% reduction in the number of migraine days; (2) the amount of complete responders, defined as patients who had 100% reduction in the number of migraine days; (3) total migraine hours; (4) acute medication treatment days; (5) migraine severity; (6) migraine-related symptom severity; (7) number needed to treat (NNT); (8) number needed to harm (NNH); (9) Migraine-Specific Quality of life questionnaire (MSQ); (10) Headache Impact Test (HIT-6); (11) Patient Global Impressions scales (PGI-S and PGI-I) and; (12) Perceived Stress Scale (PSS) (Fig. 2).

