### Study procedures

Subjects with proven menstrual migraine according to their headache electronic diary (E-diary) data or subjects who have indicated an interest via our web form will receive an information form, an informed consent form, and a response leaflet as an invitation to participate in this trial [25]. If there is no response within 2 weeks, a telephone call will be made by a researcher to provide further information. Participants will visit the LHC to determine eligibility. For this purpose, initial history (including cardiovascular risk factors and comorbidity) and neurological examination (including also blood pressure measurement) will be performed. A blood sample will also be taken to determine hormone and cholesterol status. If participants give permission, 40 ml extra blood will be collected and stored for biobanking purposes in the LUMC Biobank Headache (neurological disorders). The regulations of the LUMC Biobank Headache Collection protocol will be applicable to this biobank collection, registered under BB23.003 (the Netherlands).

After the first visit to the LHC, participants will start with a baseline period of 1 month. During the baseline period, participants start or continue filling out a daily headache E-diary. After completion of this month, remaining exclusion criteria will be checked (chronic migraine and medication-overuse headache). If a woman is found eligible, she will be randomized for either the combined oral contraceptive pill or vitamin E using Castor EDC [28]. Before the start of treatment, all participants will take a urine pregnancy test and complete questionnaires (15 min). During the baseline visit, participants will receive an invitation to fill out an online expectations questionnaire, the Stanford Expectations of Treatment Scale (SETS). This questionnaire will be used to help assess expectancy effects of both interventions. For participants whom already registered 1 month of E-diary data prior to the inclusion visit, additional baseline measurements are not needed. The questionnaires filled out during this period serve as baseline measurements for these participants.

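### The primary set is called intention-to-treat but requires at least one dose; with allocation known to all, this leaves the comparison open to post-randomisation selection of unknown, possibly negligible size

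*Protocol article*

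**What the plan says.** Under Outcome measurements, the protocol article states for the primary analysis: "An intention-to-treat approach (all participants who were randomly assigned and received at least one dose of study drug". The same section defines the safety population by the same dose condition: "Safety analysis will include all participants who received at least one dose of study drug". The only other efficacy set is narrower: "an as-treated analysis will be performed with only those participants who used study medication daily during three months". The main analysis of the primary endpoint uses no imputation. Sensitivity analyses with imputation under missing-at-random (MAR) or missing-not-at-random (MNAR) assumptions are planned.

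On knowledge of allocation, Methods says that "participants, investigators, and study personnel are aware of the treatment assignments". The one blinded party is named under Outcome measurements: "The data analyst will be blinded".

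On sequence, Study procedures says: "If a woman is found eligible, she will be randomized for either the combined oral contraceptive pill or vitamin E using Castor EDC". Treatment starts after that step, so there is an interval between allocation and first dose.

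**The concern.** Intention-to-treat means that everyone randomised is analysed in the arm assigned. Requiring a dose makes inclusion depend on something that happens after randomisation. The usual defence is blinding: if nobody knows the arm, not starting cannot depend on it.

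That defence is not available here. One arm is a hormonal contraceptive, for which the Background mentions side effects and a raised relative risk of stroke. The other is a vitamin that the Discussion describes as a placebo with limited efficacy. A woman who knows her arm can decline to start because of it, and the reasons may differ between arms. If the women who decline also differ in prognosis, the two groups analysed are no longer the two groups randomised. The direction of any bias cannot be told in advance.

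This is a rule the article fixes, not a detail left to an analysis plan. At stake is the primary comparison of a trial whose Conclusion expects its results to enter guidelines.

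**Working it through.** **Inputs from the article.** Target difference 2 days, SD 4.0 days, type I error 0.05 (two-sided, from the 1.96 in the formula), power 90%, 84 per group, raised to 90 per group for drop-out (Sample size calculation). Allocation 1:1 (Abstract).

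**Inputs assumed.** The article does not say how many women never start (k, all placed in one arm of 90) or by how many days their mean change differs from that of starters (g). Both are varied below.

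**Step 1: reproduce the plan's figure.** (1.96 + 1.28)² × (2 × 4²)/2² = 10.4976 × 8 = 83.98, so 84 per group. Unrounded quantiles give 85. Power is 0.900 at 84 per group and 0.918 at 90. The planned size is not in dispute.

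**Step 2: effect of dropping non-starters.** The all-randomised mean of the arm is the starters' mean plus (k/90) × g. Excluding non-starters therefore shifts that arm's mean by b = (k/90) × g. With no true treatment effect, SE = 4 × √(1/90 + 1/(90 − k)), and the normal approximation gives

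type I error = 1 − Φ(1.96 − b/SE) + Φ(−1.96 − b/SE).

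| k of 90 | g (days) | shift b (days) | SE | type I error |
|---|---|---|---|---|
| 2 | 2 | 0.044 | 0.600 | 0.051 |
| 4 | 4 | 0.178 | 0.603 | 0.060 |
| 6 | 4 | 0.267 | 0.607 | 0.072 |
| 9 | 4 | 0.400 | 0.613 | 0.100 |

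Against the 2-day target, the first row is 0.044/2 = 2% and the third is 0.267/2 = 13%.

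**Step 3: power cost of keeping non-starters.** Suppose all k are in the contraceptive arm and gain no effect. The difference becomes 2 × (1 − k/90). With 90 per arm:

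| k | difference (days) | power |
|---|---|---|
| 0 | 2.000 | 0.918 |
| 2 | 1.956 | 0.907 |
| 4 | 1.911 | 0.893 |
| 6 | 1.867 | 0.879 |
| 9 | 1.800 | 0.855 |

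**Step 4: do the stated safeguards close the gap?**
- The blinded analyst does not, because the exclusion follows from the participant's own decision before analysis.
- The expectation scale in the Discussion can adjust for expectations among women analysed, but it does not bring excluded women back.
- The imputation analyses are not said to add never-dosed women to the set.
- The baseline value in the primary model absorbs only the part of g that baseline migraine days predict.

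**The case against.** The strongest reply is that the effect may be trivial, and this stands. Nothing in the article suggests that many women fail to start. The larger rows in the table put all non-starters in one arm, and g = 4 is a full planned SD and twice the target difference. Moreover, g can mix prognosis with the mere absence of treatment effect in untreated women; only the prognostic part biases a comparison under the null.

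A second reply is that redefining the set gains little by itself, and this also stands. With no imputation in the main analysis, a non-starter without diary data after baseline contributes nothing under either definition. The benefit depends on continued diary follow-up. For the 106 women already included by 12 October 2023 (Trial status), follow-up that was not done cannot be recovered.

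Third, the definition is spelled out beside the label, so a careful reader can see what the set is. This is true, but it discloses the rule without removing its effect.

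A reader might go further and infer that the pregnancy test works as an eligibility check after randomisation that biases the set, since Study procedures mentions it after the randomisation step: "Before the start of treatment, all participants will take a urine pregnancy test and complete questionnaires (15 min". The text does not support that. It places the test before treatment, not after allocation, and the paragraph is not strictly chronological, since the next sentence goes back to the baseline visit. Pregnancy is a listed exclusion criterion, and only women found eligible are randomised. Against this, the checks named just before randomisation are chronic migraine and medication overuse only, so the order is unclear. Even if the test follows allocation, all participants take it, and a pregnancy that predates allocation cannot depend on the arm.

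**Conclusion.** The point holds as a wrong label on the primary set and a risk that blinding does not cover. The primary set is modified intention-to-treat, allocation is open, and the article states no analysis of all randomised women.

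It does not show that the trial is biased. The size cannot be established from the article. Under the stated assumptions (non-starters all in one arm, SD 4, normal approximation), it runs from negligible (2 of 90 differing by 2 days: about 0.04 days, type I error 0.051) to material (6 of 90 differing by 4 days: about 0.27 days, 0.072). The upper figures illustrate what many, lopsided and prognostically different exclusions would do; they are not an expected bias. The order of the pregnancy test needs clarifying and is not evidence of bias. Overall, this is a point that should be fixed, because the primary analysis rests on it and the remedy is cheap.

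**What to change.** 1. Define the primary analysis set as all randomised women, analysed in the arm assigned, whether or not a dose was taken.
2. Continue E-diary collection through weeks 9 to 12 for women who do not start. Without this the redefinition has little effect.
3. Use the dose condition for the safety set only.
4. Report never-dosed women by arm, with reasons.
5. For women already enrolled who did not start and whose diary was not continued, include them in the planned MAR and MNAR sensitivity analyses.
6. State the order of the pregnancy test and randomisation.

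The cost is a change of wording, continued diary contact with what may be few women, and slight dilution of the effect. With 4 assumed non-starters, all in the contraceptive arm and gaining nothing, power falls from 0.918 to 0.893. The planned 180 participants need not change.

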## Discussion

This article presents the rationale and design of an ongoing randomized controlled trial that aims to investigate the preventive effect of continuous daily use of ethinylestradiol/levonorgestrel (30/150 μg/day) compared with vitamin E (400 IU/day) in women with menstrual migraine. Our trial is designed to provide evidence for the effectiveness of the combined oral contraceptive pill as a preventive treatment for menstrual migraine. Vitamin E is being used as a placebo control group in this trial. The choice of vitamin E as a placebo was based on its limited efficacy in the prevention of menstrual migraine attacks and its good tolerability profile [21]. This will allow for a fair comparison between the two treatment groups while minimizing the risk of bias. To correct for the unblinded settingof the study, the Stanford Expectations of Treatment Scale will be used [29]. This scale is designed to assess the expectations of participants regarding the effectiveness of the treatment they receive. By using this scale, we can measure and adjust for any potential differences in expectations between the two treatment groups, which could influence the outcomes of the trial.

Menstrual migraine affects an important proportion of women of reproductive age, as it concerns two thirds of all women with migraine [25]. Despite the availability of prophylactic medications, many women still experience frequent attacks, particularly during the menstrual window [30]. These perimenstrual attacks are often longer of duration with increased risk of recurrence, more severe, and less responsive to acute medication [27]. Previous studies have suggested that the use of combined oral contraceptives, such as ethinylestradiol/levonorgestrel, can reduce the frequency and severity of perimenstrual migraine attacks. However, the current evidence is limited and conflicting, and the optimal dosing regimen and duration of treatment remain unclear. Therefore, this large randomized controlled trial is an imperative necessity to determine the efficacy of the continuous use of ethinylestradiol/levonorgestrel in women with menstrual migraine.

## Conclusion

The results of the WHAT! trial will have important implications for the clinical management of women with menstrual migraine and can be implemented in future guidelines and recommendations regarding the use of combined oral contraceptive pills as a preventive treatment.

## Trial status

Recruiting started on 10t September 2019. The current protocol is version 5.0 of 01 August 2022. Currently (12t October 2023), we included 106 patients. Patient recruitment is estimated to be completed around December 2024.

## Data Availability

The data that support the findings of this study are available on reasonable request from the corresponding author. Trial results will be communicated to participants, healthcare professionals, the public, and other relevant groups trough publication.

## Abbreviations

WHAT: Women, Hormones, Attacks and Treatment
COC: Combined oral contraceptives
CHC: Combined hormonal contraception
HFI: Hormone-free interval
MMD: Monthly migraine days
MHD: Monthly headache days
RCT: Randomized controlled trial
LHC: Leiden Headache Center
E-diary: Electronic diary
SETS: Stanford Expectations of Treatment Scale
SAE: Serious adverse event
AE: Adverse event
SD: Standard deviation
